#### Enrollment and randomization

2.2.3

Persons with diabetes will be introduced about the study at society meetings and at social media. Potential study participants that are suitable (according to the study criteria) for the study will be contacted and informed in more details about the study by the research nurses. Furthermore, a welcome letter will be sent by post to the participants with practical information. If acceptance and pass of criteria, informed consent form will be signed and the potential participants will be recorded in the research software program Research Electronic Data Capture® (REDCap) version 13.1.37. The participants will then be randomized and will adhere to the clinical study schedule and specific study procedures. The enrolled study participants will be given an autonomic code (in REDCap) as soon as the participants have signed the consent form. According to the code the participants will be randomized into different treatment, unknown which, for both the participants and the investigators (double-blind). Apart from the treatment randomization the participants will be randomized to which foot that will be treated with which cream. One foot will be treated with one interventional cream (cream A or B) and the contralateral foot with the comparator humectant-free cream (C).

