##### Package

2.2.6.1

All three creams will be filled into similar pump containers to ensure the blinding process. The filled containers will be packed as kits. Each kit will contain two containers, with two different creams, either Oviderm together with Decubal lipid cream or Canoderm together with Decubal lipid cream. One of the kit type will be given to each participant after the randomization procedure.

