### Statistical analysis

2.5

The primary analysis principle applied will be the intention-to-treat. All statistical analysis and data management will be performed using SPSS for Windows, version 28.0 (IBM, Armonk, NY, USA). Measurements, such as XSS score, TEWL, pH, impedance, abundance of the biomarkers will be used as continuous variables and treatment with the creams, gender, and patients grouping parameters will be used as categorical variables. Descriptive statistics such as number of participants, mean, median, standard deviation, minimum and maximum values will be summarized and tabulated. XSS score will be independently evaluated by a random sample of twenty photographs by a second dermatologist, for validation purposes, to be able to assess inter-rater reliability by calculating intraclass correlation with 95 % confidence intervals. The primary outcome of the study is to compare the change in XSS score from baseline until the end (4 weeks) due to treatment with moisturizing creams vs a comparator product. Prior to analysis of the XSS differences between the treatment groups, the distribution of the data will be tested for normality by performing Shapiro-Wilk and Kolmogorov-Smirnov tests, as well as inspecting quantile-quantile (QQ) plots. Homogeneity of variances will be tested by performing Levene's test. Comparison between two related groups, *e.g.*, application of the formulation on the left and right foot, will be done by paired two-sample *t*-test, whereas for unrelated two groups two-sample *t*-test will be performed. When neither homogeneity of variances nor assumption of normality will be fulfilled, a non-parametric Wilcoxon rank sum test will be applied. In case of comparison between more than two groups, *e.g.*, the effect of three creams, one-way ANOVA with multiple comparisons (Tukey's test) will be used. Alternatively, if assumptions of normality or homogeneity of variances will not be fulfilled, non-parametric Kruskal Wallis test will be performed. The effect of covariables, *e.g.*, age, on main effect, *e.g.*, XSS change upon the treatment with the cream, will be tested by performing ANCOVA analysis. To seek for the measurements capable to explain and predict the effectiveness of the diabetic foot treatment with different creams more complex statistical analysis will be performed. Principal component analysis (PCA), multiway ANOVA and mixed models, and multiple regression analysis and model selection will be performed on the data collected. Level of statistical significance was set to p<0.05.

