## Discussion

3

The prevalence of diabetes mellitus is increasing in the world, 537 million adults suffer from this condition, and it is estimated to raise [1]. DFU is a devasting complication, ending up in major amputation and shorter life-expectancy for many. Prevention for DFU is therefore a global priority.

Better foot care with hydration may result in healthier feet but also to better vigilance of foot status in persons with diabetes. To be able to show differences in change in skin xerosis when using creams containing humectant compared with humectant-free cream on dry feet in persons with diabetes, might lead to specific recommendations for products that can be used for prevention of DFU. Furthermore, the results of this study can fill the gap of lack of documented effect when using different creams for persons with diabetes.

A potential limitation of this RCT could be that persons with diabetes accepting and attending this study is among those with most healthy feet in a population of diabetes, a well-known phenomenon in population-based screening studies [31]. Consequently, there is a risk that XSS scores at baseline are at the lower range, close to 2, where there is not much room for improvement by intense foot hydration with any of the creams. Determination of XSS scores is not always clear-cut and there may be discrepancies between raters. Therefore, we plan to perform an inter-rater reliability assessment, where twenty randomly selected photographed feet are selected and assessed by two independent dermatologists. The study protocol with at least three visits may for some participants be difficult to comply with, and there is a risk for attrition bias, where persons living far away from the centrally located research centre in Malmö, or elderly with higher degree of comorbidity, drop out from the study. The strengths are the design of two-armed double-blinded RCT, where the patients both feet are randomized, one receiving one of the intervention creams and the contralateral foot by default receiving the comparator cream. In this way, the participants feet act as a perfect matched pair of intervention-control, where patient-related factors are identical. Comprehensive evaluation of skin integrity barrier, microcirculation and neuropathy during the study period will hopefully result in advance in the understanding of disturbances of dry feet in persons with diabetes, and how to counteract.

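### The three-cream comparison uses tests for independent groups although every comparator foot shares a person with an intervention foot; the error is conservative and does not touch the paired primary tests

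*Protocol article*

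**What the plan says.** The Statistical analysis section (2.5) sets the rule for comparing more than two groups, and its own example is the three creams: "one-way ANOVA with multiple comparisons", by Tukey's test. If normality or equal variances fail, a "non-parametric Kruskal Wallis test will be performed".

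The same section treats two related groups differently: a comparison such as "application of the formulation on the left and right foot, will be done by paired two-sample *t*-test". Mixed models appear later in 2.5, but only among the analyses meant to explain and predict effectiveness. They are not assigned to the three-cream comparison.

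The design is paired. Under Enrollment and randomization (2.2.3), one foot receives cream A or B and the other receives C. Under Package (2.2.6.1), each kit holds "either Oviderm together with Decubal lipid cream or Canoderm together with Decubal lipid cream". The Discussion presents this as a strength: "the participants feet act as a perfect matched pair of intervention-control, where patient-related factors are identical".

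**The concern.** One-way ANOVA, Tukey's test and Kruskal-Wallis assume that all observations are independent, and none of them has a term for the person. Here every C foot belongs to someone who also contributes an A foot or a B foot. The section keeps the pairing when it compares two feet and drops it when it compares three creams, although two of the three contrasts (A vs C and B vs C) are within-person.

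At stake is how the three-cream result is read. If the two feet of a person are positively correlated, as the matching argument in the Discussion presumes, the overall test and the contrasts with C rest on too large an error, so a non-significant result could come from the choice of test. Tukey would also print A vs C and B vs C a second time, beside the paired tests, and the section does not say in so many words which of the two counts.

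**Working it through.** **Inputs from the protocol.** Sample size estimation (2.2.4): SD of the within-person difference 2.0, difference to detect 1 XSS point, two-sided 0.025 per comparison, 80 % power, 39 evaluable persons per arm. Section 2.5: significance level 0.05, used here for the overall test and for Tukey. The design gives 39 A feet, 39 B feet and 78 C feet.

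**Assumption.** The correlation ρ between the two feet of a person is not stated. I vary it from 0 to 0.7 and hold the SD of the difference at 2.0, so the SD of a single foot's change is σ = 2/√(2(1−ρ)). Outcomes are simulated as normal with equal variances, an approximation for a 7-grade scale.

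**The plan's own figure.** N = 2.0² × (2.2414 + 0.8416)² / 1² = 38.02, so 39 per arm, 78 in total, and 78/0.8 = 97.5, so 98. This reproduces and rests on the paired difference. (Section 2.2.4 prints 2.1414 for the first quantile, which would give 35.59, so 36. The stated 39 fits 2.2414, so this looks like a misprint and is separate from this point.) With the t rather than the normal distribution, 39 pairs give 78 % power.

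**Contrasts with C.**
- ANOVA assumes variance σ²(1/39 + 1/78) = 3σ²/78.
- The 39 A feet each share a person with one of the 78 C feet, so the two means have covariance ρσ²/78. The true variance is (3 − 2ρ)σ²/78.
- The ratio of standard errors (SE) is √(3/(3 − 2ρ)). At ρ = 0.5: √(3/2) = 1.22.

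**A vs B.**
- These feet belong to different persons, so the ANOVA variance 2σ²/39 is correct.
- A model with a person effect also uses each person's C foot and reduces the variance to 2σ²(1 − ρ²)/39. At ρ = 0.5 the SE falls from 0.453 to 0.453 × √0.75 = 0.392, which is 25 % less variance.

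| ρ | Foot SD | A vs C: ANOVA SE | A vs C: true SE | Too wide by | A vs B: ANOVA SE | A vs B: person-effect SE |
|---|---|---|---|---|---|---|
| 0 | 1.41 | 0.277 | 0.277 | 0 % | 0.320 | 0.320 |
| 0.3 | 1.69 | 0.331 | 0.296 | 12 % | 0.383 | 0.365 |
| 0.5 | 2.00 | 0.392 | 0.320 | 22 % | 0.453 | 0.392 |
| 0.7 | 2.58 | 0.506 | 0.370 | 37 % | 0.585 | 0.418 |

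B vs C is the same as A vs C by symmetry.

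**Error rate and power**, by simulation (20,000 trials per setting; 2,000 for Kruskal-Wallis). Rejection rates are under no difference, at nominal 5 %. Power is for a 1-point effect of A and B over C.

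| ρ | Overall F test rejects | Kruskal-Wallis rejects | Tukey power, A vs C | Paired t power at 0.025 |
|---|---|---|---|---|
| 0 | 5.0 % | 4.6 % | 89 % | 78 % |
| 0.3 | 3.1 % | 3.2 % | 76 % | 78 % |
| 0.5 | 2.1 % | 2.8 % | 59 % | 78 % |
| 0.7 | 1.7 % | 1.6 % | 30 % | 78 % |

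**Break-even.** Tukey's critical value is 2.367. At ρ = 0.28, σ = 1.667, the ANOVA SE is 0.327 and the true SE 0.295. Power is then about Φ((1 − 2.367 × 0.327)/0.295) = Φ(0.77), or 78 %, equal to the paired test. Below that correlation Tukey has the higher power, because it uses all 78 C feet.

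**The case against.** The best defence is that the three-cream analysis is not the primary one. Section 2.5 sends left-versus-right comparisons to the paired t-test, 2.2.4 sizes the trial on two paired comparisons, and Intervention (2.3) evaluates each humectant cream against the comparator within its own arm. This stands, and it rules out several stronger readings:

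- *The primary analysis is invalid, or two conflicting primary answers are planned.* The text already names the paired test for related feet. Tukey would repeat A vs C and B vs C, so the overlap is real, but ANOVA is reserved for more than two groups. The 59 % against 78 % would be a loss to the trial only if Tukey replaced the paired test, which the protocol does not say.
- *False positives are inflated.* With positive correlation they become rarer.
- *All standard errors are wrong.* The one for A vs B is valid, and A vs B is the only contrast that this analysis adds to the paired tests.
- *Power is always lost.* At ρ = 0 there is no error, and at 0.3 the two powers are nearly equal. The 0.7 row implies a foot SD of about 2.6, which is hard to credit on a 0 to 6 scale.

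A second defence is that mixed models are already listed in 2.5. They are, but for explanatory work, while the three-cream comparison has its own named test. That test is stated in the protocol, so this is not a detail left to an unseen analysis plan.

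**Conclusion.** The point holds in a limited form. The named tests do not fit the paired structure: the overall test and the Tukey contrasts with C use the wrong error term, and Kruskal-Wallis has the same fault. For correlations of 0.3 to 0.5 the SE of those contrasts is 12 % to 22 % too wide, and the nominal 5 % overall test rejects about 2 % to 3 % of the time under no difference. A vs B loses precision but not validity. The size depends on a correlation that the protocol does not give and on the SD of 2.0 for the difference. The paired primary tests and the sample size stand. This should be corrected, but it does not threaten the main conclusion.

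**What to change.** In section 2.5:

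1. State that the two within-person contrasts, A vs C and B vs C by paired t-test at 0.025 each, are the sole primary analysis.
2. For the three-cream comparison, replace one-way ANOVA with Tukey by a linear mixed model on foot-level change, with cream and foot-level baseline as fixed effects and participant as random effect. Label it secondary and use it mainly for A vs B, so that its own A vs C and B vs C estimates do not compete with the primary ones.
3. Replace the Kruskal-Wallis fallback by rank methods that respect the pairing: Wilcoxon signed-rank for A vs C and B vs C, and a rank-sum test of the within-person differences for A vs B.
4. If any ANCOVA is run on foot-level data, include the participant effect. The section does not say whether its ANCOVA uses feet or within-person differences.

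The cost is a wording change and some extra analysis work. Mixed models are already in the plan, and neither data collection nor sample size changes.

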##### Secondary outcomes

2.3.1.2

The secondary outcomes are supporting evidence of differences in efficacy of creams on skin barrier integrity, and changes in health-related quality of life during the study period. Skin barrier integrity and hydration will be obtained by non-invasive biophysical measurements as follows.•Trans epidermal water loss (TEWL) is a key indicator of the barrier function of the stratum corneum (SC). Elevated TEWL typically indicates a compromised skin barrier, while lower TEWL is associated with good SC barrier properties and healthy skin [24].•Skin hydration by measurement of skin impedance (skin resistance and skin capacitance). It is well-known that maintaining healthy skin relies heavily on adequate skin hydration [25]. Standard methods for assessing skin hydration involve measuring the skin's electrical properties, which vary with the skin's water content. In this work, the skin hydration will be assessed by measuring the resistance and capacitance by electrical impedance spectroscopy [26]. Increased skin capacitance (increased dielectric constant of skin) indicates higher skin hydration; thus healthier skin barrier [26].•Skin surface pH provides an indication of host-microbiota interaction. Acidic pH value (*e.g.*, pH 5.5) is usually related to the dominance of commensal bacteria on the skin. Shifting skin surface pH towards basic values (*e.g.*, pH 6.8) might indicate an increased inhabitance of skin by pathogenic microbiota [27].•Health related quality of life assessed with EuroQoL 5 level (EQ-5D-5L) instrument.

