To support the outcomes by molecular characteristics of skin and physiological health parameters relevant to diabetes the following assessments will be made.•Macrocirculation measured as ankle-brachial index and toe-brachial index. Microcirculation including transcutaneous oxygen pressure (Laser doppler/transcutaneous O_2_ -electrode/laser doppler flow with heat provocation) (Peripheral circulation is measured by Periflux 6000 combined; Perimed AB, Stockholm, Sweden)•Degree of neuropathy (multi-frequency vibrametry) (VibroSense Meter; VSM II, Vibrosense Dynamics AB, Malmö, Sweden). Assessment of vibration perception threshold at 125 Hz with multi-frequency vibrometry has shown to have a strong correlation with nerve conduction studies in diabetic peripheral neuropathy [28].•Molecular biomarkers including microbiota will be analyzed after a non-invasive sampling from the surface of the skin.•HbA1c by using a stick test for collecting capillary blood in the middle finger.•XSS scores are determined by study investigators at study inclusion and will be validated by a dermatologist. Photographs of the feet will be taken to validate XSS grading and for documentation of the colour and surface structure of the skin.

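### The search for predictors of effectiveness pairs regression model selection with a plain p<0.05 rule, which does not hold its 5% level after selection; how far it misses depends on choices the article does not state

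*Protocol article*

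**What the plan says.** Section 2.5 (Statistical analysis) gives the aim of the exploratory modelling: "To seek for the measurements capable to explain and predict the effectiveness of the diabetic foot treatment with different creams". Principal component analysis, multiway ANOVA and mixed models are listed as tools, and the section then closes with the regression and the significance level side by side: "multiple regression analysis and model selection will be performed on the data collected. Level of statistical significance was set to p<0.05". The section names no selection algorithm, no candidate list and no separate rule for these models.

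On what could enter the models, section 2.5 says that "Measurements, such as XSS score, TEWL, pH, impedance, abundance of the biomarkers will be used as continuous variables". Section 2.3.1.2 (Secondary outcomes) adds "Skin hydration by measurement of skin impedance (skin resistance and skin capacitance" and a further group introduced by "To support the outcomes by molecular characteristics of skin and physiological health parameters relevant to diabetes the following assessments will be made": macro- and microcirculation, neuropathy, molecular biomarkers with microbiota, and HbA1c. Section 2.4 (Data management) adds year of birth, gender, diabetes type and year of diagnosis. Section 2.2.4 (Sample size estimation) plans 39 evaluable persons per arm, 78 in total. Its 2.5% level is tied to the two comparisons of an intervention cream with the comparator.

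**The concern.** A regression p-value assumes that the model was fixed before the data were seen. Under that assumption, a predictor with no association falls below 0.05 in 5% of trials. Once a routine has searched many candidates and kept those that look best, the printed p-value belongs to a winner of the search, and the 5% no longer applies. There are two sources of error: many predictors are examined, and the selection step favours those that look strong by chance. The apparent R-squared of the selected model is too high for the same reason.

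At stake is any statement that a skin, circulation, nerve or molecular measurement predicts response to a cream. Section 3 (Discussion) hopes that these measurements will improve understanding of dry feet in diabetes, and a chance predictor could be taken up in that account.

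**Working it through.** **Sample size used as input.** Section 2.2.4 gives N = SD² × (λα + λβ)² / Δ², with SD 2.0, Δ 1, two-sided 0.025 and 80% power. This is 4 × (2.2414 + 0.8416)² = 38.02, rounded up to 39 per arm and 78 in total; 78/0.8 = 97.5, hence 98. The planned 39 is therefore reproduced. (The article prints λα as 2.1414, which would give 35.59, so 36; the stated 39 corresponds to 2.2414. This does not affect the present point.)

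**Candidate count from the article.**
- Skin: TEWL, resistance, capacitance, pH (4)
- Quality of life: EQ-5D-5L (1)
- Circulation: ankle-brachial index, toe-brachial index, transcutaneous oxygen, laser Doppler flow, flow with heat provocation (5)
- Vibration threshold (1) and HbA1c (1)
- Biomarkers and microbiota, counted as only 2

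Subtotal 4 + 1 + 5 + 2 + 2 = 14. Adding age, gender, diabetes type, duration, baseline XSS and cream gives 20. Single biomarkers or taxa would come on top.

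**Simple benchmark.** For k independent tests at 0.05, the chance of at least one false positive is 1 − 0.95^k: 23% for k = 5, 40% for 10, 51% for 14 and 64% for 20.

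**Simulation with no true association.** A normal response was generated independently of k candidates, with pairwise correlation 0 or 0.3 among the candidates, n = 39 or 78, and 800 runs per cell. Three selection routines were assumed: stepwise (entry p<0.05, removal p>0.10), backward elimination (removal p>0.10) and backward AIC. The table gives the percentage of runs with at least one p<0.05 predictor in the final model, as the range over both n and both correlations. The column without selection counts p<0.05 in the full model.

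| k | No selection | Stepwise | Backward | AIC |
|---|---|---|---|---|
| 5 | 19-21 | 19-21 | 22-26 | 23-28 |
| 10 | 33-39 | 33-39 | 43-51 | 46-57 |
| 14 | 39-48 | 46-52 | 57-70 | 62-77 |
| 20 | 48-61 | 58-64 | 74-88 | 80-93 |

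The simulation error of a cell near 50% is √(0.5 × 0.5/800) = 1.8 percentage points.

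Much of the excess is already there without selection, because many coefficients are each read at 0.05. Backward and AIC selection add most to it. A single global F-test of the full model stayed near its level in the same runs (3.6% to 6.6%).

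**Apparent fit.** In a separate simulation (400 runs, same stepwise rule, 18 candidates), at least one p<0.05 predictor appeared in 50-60% of runs with n = 39 and 54-64% with n = 78. When something was selected, mean R-squared was about 0.21 and 0.11 respectively; the true value was 0.

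**The case against.** The strongest reply is that the procedure is partly inferred. The p<0.05 sentence closes the whole section, after the t-tests, rank tests, ANOVA and ANCOVA, and reads as a general convention. Model selection could rest on an information criterion or on cross-validation. The article does not say that p-values from the selected model will be offered as proof of prediction. The algorithm, candidate list and validation step are details that a condensed article may leave to a fuller document, so their absence is not a fault. Principal component analysis is named alongside the regression and might reduce the candidates first. The purpose is exploratory, prediction is not among the stated objectives, and section 2.2.4 claims family-wise control only for the two cream comparisons.

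Most of this stands, and it limits the size of the point. A reader might infer that the plan will produce a false predictor half the time or more. The article does not support that as a general statement: with 5 candidates the rate is 19-28%, with 10 under stepwise selection 33-39%, and nothing says that all named measurements enter one model. A reader might also infer that an inflated R-squared will be reported; the article never mentions R-squared.

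One part does not stand. The section states a significance level, gives no exemption for the selected models, and offers no other rule for them. Choosing AIC would not help, since its rate of p<0.05 predictors was the highest of the three routines. The article also does not say that principal components will feed the regression.

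**Conclusion.** The point holds in conditional form. As written, the only stated rule for the predictor search is p<0.05, and that rule does not have a 5% error rate after data-driven selection. For the roughly 14 to 20 candidates the article names, the chance of at least one spurious predictor is 46-93%; a short list or prior dimension reduction would bring it down, though at 5 candidates it is still about four to five times nominal. These figures assume no true association, a roughly normal response, candidate correlations of 0 to 0.3 and one of the three routines tested.

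Importance is minor to moderate. The search is exploratory, and neither the primary comparison of XSS change nor a recommendation built on it is affected. It would be wrong to read this as a threat to the trial's main conclusion.

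**What to change.** Add to section 2.5, or to the analysis plan that supersedes it, wording such as: *The search for predictors of treatment effectiveness is hypothesis-generating. The p<0.05 level does not apply to p-values from a selected model, and these are not presented as evidence. The whole selection procedure is repeated within bootstrap or cross-validation, and optimism-corrected R-squared and selection frequencies are reported. A predictive claim is made only if a test valid for the whole search is below 0.05.*

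That test could be a permutation test that reshuffles the response across persons and repeats the selection each time, or a global F-test of a full prespecified model. The F-test suits only a limited list: with 39 persons and 20 candidates it leaves 39 − 20 − 1 = 18 residual degrees of freedom, and it cannot take in a large set of taxa. If the arms are pooled, permuting within arm keeps a difference between creams from counting as a predictor. Penalised regression is one option for the selection step and is not required.

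The cost is wording and computing time, with no new data or visits. Some of the resampling may need tools outside base SPSS, although the section says that "All statistical analysis and data management will be performed using SPSS for Windows, version 28.0", so that sentence may need widening. Fewer predictors will be declared, and the reported fit will look less favourable.

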**Methods:**

Two-armed double-blind RCT, registered in ClinicalTrials.gov Identifier: NCT06427889. With 80 % power, two-tailed significance of 2.5 % in each arm, 39 study persons is needed in each arm, total 78 persons, 98 including dropouts, to be able to prove a reduction of at least one category in the Xerosis Severity Scale with the intervention creams compared to the comparator. In one arm, each participant will treat one foot with one of the intervention creams (Oviderm® or Canoderm®), while the opposite foot will be treated with the comparator cream (Decubal®lipid cream), twice a day. If needed, participants are enrolled after a wash-out period of two weeks. The participants will undergo examinations at baseline, day 14 and day 28.

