#### Sample size estimation

2.2.4

This is a superiority RCT, where either of the intervention creams is hypothesized to be superior to the comparator cream in reducing XSS score during a four-week application period. To be able to prove this hypothesis, a total of 98 participants, 39 persons with diabetes in each arm for analysis, is needed, which is based on the following: A change in XSS score ≤1 is not regarded clinically important. The estimated intra-individual standard deviation for the difference in XSS score is 2.0. With 80 % power, two-tailed significance of 2.5 % in every arm, 39 evaluable study persons is needed in every arm, a total of 78 persons. If 20 % of persons are estimated not to be fully evaluable, sample size increases to 98 (78/0.8).

The following formula will be used to calculate the number of patients needed in each part of the trial [15,16] (N = number of fully evaluable patients in each part of the trial):$$N=\frac{\sigma_{d}^{2}\times {\left(\lambda_{\alpha }+\lambda_{\beta }\right)}^{2}}{\Delta^{2}}$$In the formula above σ_d_ is the standard deviation for the difference between the change in each treatment, Δ is the difference to detect between the treatments (a difference of at least 1 is assumed to be clinically relevant), λ_x_ is the x:th percentile of the standardized normal distribution. As the test is two-sided and the significance level should be 0.0250 (in order to keep the family-wise type I error at 5 % and there are two comparisons: Canoderm® versus Decubal® and Oviderm® versus Decubal) then λ_α_ = 2.1414. If the power is 80 % then λ_β_ = 0.8416 and if the power is 90 % then λ_β_ = 1.2816.

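### Section 2.5 sets significance at p<0.05, but section 2.2.4 requires 0.025 for each of the two primary comparisons; followed as written, 2.5 gives a family-wise error of 9.75 % instead of the promised 5 %

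*Protocol article*

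**What the plan says.** Section 2.2.4 (Sample size estimation) fixes the level for the primary tests: "As the test is two-sided and the significance level should be 0.0250". It gives the reason: "in order to keep the family-wise type I error at 5 % and there are two comparisons", and names them as Canoderm against Decubal and Oviderm against Decubal. The same section states "With 80 % power, two-tailed significance of 2.5 % in every arm, 39 evaluable study persons is needed in every arm", and the abstract (Methods) repeats the 2.5 % level for each arm.

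Section 2.5 (Statistical analysis) identifies the primary outcome as the change in XSS score from baseline to four weeks and assigns the paired t-test to comparisons between a participant's two feet. It then covers the group comparisons, covariate analyses and exploratory models, and closes with "Level of statistical significance was set to p<0.05". It does not mention 0.025, does not refer back to section 2.2.4 and does not exempt the two primary comparisons. Its only multiplicity device, Tukey's test, is reserved for comparisons of more than two groups.

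**The concern.** One primary analysis has two thresholds. An analyst working from section 2.5 would test each primary comparison at 0.05; one working from section 2.2.4 would use 0.025. The trial has two chances of a positive primary result, and the split of alpha in section 2.2.4 exists to pay for the second. If section 2.5 governs, that protection is lost and the stated 5 % family-wise error is not kept. A primary p-value between 0.025 and 0.05 could be called a success or a failure depending on which section is cited, and that choice could be made after the result is known.

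**Working it through.** **Inputs**
- SD of the within-person difference: 2.0 (section 2.2.4: "The estimated intra-individual standard deviation for the difference in XSS score is 2.0").
- Difference to detect: 1 XSS point (section 2.2.4: "a difference of at least 1 is assumed to be clinically relevant").
- Power: 80 %, z = 0.8416 (section 2.2.4).
- Two-sided level per comparison: 0.025 (section 2.2.4 and abstract) or 0.05 (section 2.5).
- Each participant is in one arm and receives an intervention cream on one foot and the comparator on the other (section 2.2.3). No participant and no comparator foot is shared between the two comparisons.

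**Step 1: which level the sample size uses.** The formula in section 2.2.4 is N = SD² × (z_alpha + z_beta)² / difference².
- At two-sided 0.025, z_alpha = 2.2414: N = 4 × (2.2414 + 0.8416)² = 38.02, rounded up to 39. This is the plan's figure; 2 × 39 = 78, and 78/0.8 = 97.5, rounded up to 98.
- At two-sided 0.05, z_alpha = 1.9600: N = 4 × (1.9600 + 0.8416)² = 31.40, rounded up to 32. This does not reproduce 39.

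The design therefore rests on 0.025. (The quantile printed in section 2.2.4, 2.1414, would give 35.59, rounded up to 36. The 39 was evidently computed with 2.2414. That is a separate point and does not affect this one.)

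**Step 2: family-wise error.** For two independent tests with both null hypotheses true, it is 1 - (1 - alpha)².
- At 0.05 each: 1 - 0.95² = 0.0975.
- At 0.025 each: 1 - 0.975² = 0.0494.

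A simulation of 200,000 trials, each with two independent paired t-tests on 39 normally distributed differences, gave 9.6 % and 4.8 %.

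**Step 3: the disputed zone in XSS points.** The smallest significant observed mean difference is t × SD/√N, with 38 degrees of freedom and SD/√N = 2.0/√39 = 0.320.
- At 0.025: 2.334 × 0.320 = 0.747.
- At 0.05: 0.648.

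With an observed SD of 2.0, a mean difference between about 0.65 and 0.75 points is significant under section 2.5 and not under section 2.2.4.

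**The case against.** The strongest reply is that the specific rule overrides the general one. Section 2.2.4 names the two comparisons, sets their level and explains why. The sentence in section 2.5 comes at the end of a long paragraph, directly after the exploratory models, and can be read as a default for everything else. It also equals the overall level in section 2.2.4. On that reading the plan is coherent and the inflation never occurs. This reading is possible and probably reflects the intention, but no section states it, and the paragraph that the sentence closes includes the primary XSS comparison.

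A second reply is that this is a condensed article and the multiplicity procedure may be in an unseen SAP. That would answer a complaint about missing detail. It does not answer this one: the article states a threshold, and it conflicts with another threshold in the same article.

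A third reply is that the consequence is narrow, because differences of 0.65 to 0.75 points lie below the 1 point that the plan itself regards as clinically relevant. The arithmetic is right for an SD of 2.0 and limits the clinical weight of a disputed result. The zone scales with the observed SD, however, and the plan's tests are against no difference, so a statistical claim of superiority could still be made there.

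Finally, section 2.2.4 states a hypothesis about either cream, not a formal trial-level success rule. That is fair. The concern does not need such a rule, since the plan itself promises a 5 % family-wise error over the two comparisons.

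**Conclusion.** The concern holds. The article states two incompatible thresholds for its primary tests, and the one in the analysis section does not deliver the error rate that the sample-size section promises. If section 2.5 is followed as written, the family-wise error is 9.75 %, nearly double the 5 % promised; at 0.025 each it is 4.94 %. These figures assume that both null hypotheses are true, that the two arms are independent (which the design provides) and that each test holds its nominal level. The inflation is conditional on applying 0.05 to each primary comparison; the contradiction is not. It bears on whether the primary claim is met, so it must be resolved.

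**What to change.** Replace the last sentence of section 2.5 with wording such as: *Each of the two primary comparisons (Oviderm vs Decubal and Canoderm vs Decubal; change in XSS score from baseline to week 4) is tested two-sided at 0.025 and reported with a 97.5 % confidence interval. All other tests use a nominal two-sided level of 0.05 and are supportive.*

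A bare exception clause referring to section 2.2.4 would also remove the contradiction. Holm's procedure at an overall 0.05 is an acceptable alternative: it keeps the family-wise error at 5 % and is at least as powerful. Whichever is chosen, the SAP should carry the same rule, fixed before unblinding.

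The cost is one sentence. The sample size stays at 39 per arm, because it already assumes 0.025, and data collection does not change.
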